#### Implementation

We will conduct time-motion studies wherein the program coordinator will follow a random 5% of women/couples offered the intervention through their flow of clinical care to record provider/promoter time, patient wait times, and regular clinical operation disruptions. We expect that < 20 min/day will be required by nurses/counselors to deliver the PPFP intervention. During these time-motions studies, we will also assess the implementation fidelity defined using the empirically tested Conceptual Framework for Implementation Fidelity [23, 24] as the proportion of providers adhering to the intervention protocol content as assessed using a standardized checklist of key implementation steps. We expect that the intervention will be implemented per protocol in 90% of observations. The time-motion studies, inclusive of fidelity assessments, will be conducted at month 2 and at 6 months after implementation with re-training as necessary.

#### Maintenance

##### Woman/couple level

We will abstract clinic logbook data to calculate the proportion of women who are still using the PPFP method 9 months after uptake. We will conduct individual in-depth interviews with PPFP users and non-users who received the intervention and their male partners 9 months after receiving promotions. Participants identified from PPFP logbooks will be interviewed at the clinic to gain insight into women’s and men’s experiences regarding PPFP side effects, reasons for uptake/continued use/non-use, service delivery environment, demand creation strategies, and PPFP methods.

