### Eligibility criteria {10}

Aim 1: Provider and stakeholder in-depth interviews

All participants will be government employees of at least 18 years of age who provide written informed consent to participate in in-depth interviews.

Aim 2: Implement PPFP services in a cluster-randomized stepped-wedge trial

Eligible PPFP providers will be women working in L&D or family planning at one of the study facilities. Eligible Happy Client promotors will be postpartum women who received promotions and selected a PPFP method. Eligible nurse and CHW promotors will be women working as nurses or CHWs at one of the intervention facilities. All women eligible for PPFP services in this study will be at any stage of pregnancy or up to 14 weeks postpartum and receiving ANC, L&D, IV, or postpartum services at one of the intervention facilities.

Aim 3: Client/couple, provider, and stakeholder in-depth interviews

All participants will be at least 18 years of age who provide written informed consent to participate in the in-depth interviews. Clients/couples will be those who received PPFP counseling. Providers and stakeholders will be government employees.

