#### Follow-up procedures

PPFP follow-up appointments will be scheduled 6 weeks after insertion to correspond with the first IV visit. Women will be asked to self-report the side effects including signs of infection, and for PPIUD users, IUD string placement will be checked via bimanual pelvic exam. IUD strings will be trimmed as needed and a pelvic ultrasound given if the strings are not visible during physical exam. Women may decide to discontinue or request a new family planning method of their choice at any time.

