### Outcomes {12}

RE-AIM will guide outcome assessment (Table 1).

**Table 1 Tab1:** RE-AIM domains and measures

Domains	Outcome measures	Data source
**Reach**	^a^Stakeholders engaged and PPFP providers/promoters trained	Advocacy and training study log
	^a^Couples/clients receiving information about PPFP	PPFP logbook
**Effectiveness**	^a^Clients receiving PPFP/PP LARC methods PPFP side effects	PPFP logbook
**Adoption**	^a^Providers/promoters providing PPFP	Advocacy and training study log
**Implementation**	Provider/promoter time to provide PPFP Patient wait times to receive PPFP Implementation fidelity	Time motion studies, fidelity checklist
**Maintenance**	Woman/couple-level: continued PPFP use at 9 months, factors associated with PPFP uptake and continued use	Interviews, PPFP logbook
	Provider/facility-level: progress toward institutionalizing PPFP, factors associated with PPFP continued provision at the end of implementation	Interviews, standardized checklist
	Stakeholder-level: progress of the Ministry of Health to nationalize PPFP services at the end of implementation	Interviews

^a^Quantitative outcomes used in power analyses, see Table 5

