### Participant timeline {13}

The timeline in Table 2 indicates the schedule of interviews and intervention implementation. Women will participate for a maximum of 54 weeks (40 weeks gestation plus 14 weeks postpartum), and in-depth interviews with women will occur 9 months after PPFP promotions. The timeline for implementation of the cluster-randomized stepped-wedge is shown in Table 3.

**Table 2 Tab2:** Overall timeline of study activities by year (Y) (in 6-month intervals)

Aim	Study activity	Y1-1	Y1-2	Y2-1	Y2-2	Y3-1	Y3-2	Y4-1	Y4-2	Y5-1	Y5-2
1	Protocol development and IRB approvals	*X*									
	In-depth interviews		*X*								
	Facility needs assessments			*X*							
	Implement the intervention in a randomized stepped-wedge design and collect effectiveness and implementation data			*X*	*X*	*X*	*X*	*X*			
2	Evaluate intervention reach, effectiveness, and adoption								*X*	*X*	*X*
	Evaluate the intervention implementation (time-motion studies)			*X*	*X*	*X*	*X*	*X*			
	Evaluate intervention maintenance: women/couples			*X*	*X*	*X*	*X*	*X*			
	Evaluate the intervention maintenance: providers and stakeholders								*X*	*X*	
3	Develop costing tools	*X*	*X*								
	Collect cost data			*X*	*X*	*X*	*X*	*X*			
	Cost-effectiveness analyses and development of costed implantation plan								*X*	*X*	*X*
	Publications, dissemination								*X*	*X*	*X*

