## Data collection and management

### Plans for assessment and collection of outcomes {18a}

The number of stakeholders engaged and providers trained and certified will be recorded in an Advocacy and Training logbook. CHW counseling activities will be measured on referral slips which will record if a male partner was present. Women/couples receiving one-on-one PPFP counseling will have their method of interest, whether a male partner was present, household income, and estimated date of delivery recorded in a PPFP logbook, developed by the study team during the pilot and maintained by government clinic staff. The PPFP logbook will also record PPFP uptake and, among PP LARC users, provider perception of ease of insertion, client anxiety during insertion, and client pain during insertion (scales of 1–10). During follow-up visits, the PPFP logbook will record PPFP side effects and method failures. Facility information, client’s age, and parity will be abstracted from government Family Planning logbooks.

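### Continued use at 9 months is promised from logbook data, but no scheduled follow-up and no named follow-up field captures it for method users

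*Protocol article*

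**What the plan says.** Table 1 of the protocol article, under Outcomes {12}, lists as a Maintenance measure "Woman/couple-level: continued PPFP use at 9 months, factors associated with PPFP uptake and continued use", with data source "Interviews, PPFP logbook". The woman/couple-level text under Maintenance gives the method: "We will abstract clinic logbook data to calculate the proportion of women who are still using the PPFP method 9 months after uptake".

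Four other parts of the protocol bear on whether this can be done:

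- **Follow-up procedures:** "PPFP follow-up appointments will be scheduled 6 weeks after insertion to correspond with the first IV visit". No later follow-up time point is given.
- **Participant timeline {13}:** "Women will participate for a maximum of 54 weeks (40 weeks gestation plus 14 weeks postpartum". Table 2 in the same section ends the woman-level maintenance evaluation in Y4-1, the half-year in which implementation also ends.
- **Plans for assessment and collection of outcomes {18a}:** "During follow-up visits, the PPFP logbook will record PPFP side effects and method failures". Current use, removal, expulsion and switching are not named.
- **Interviews:** Table 4 plans 25 women/couples. The Maintenance text includes users and non-users and sets the interview "9 months after receiving promotions", not after uptake.

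**The concern.** The outcome is a proportion of all women who took up a method, measured at a fixed time after uptake. To estimate it, each woman's status at about that time must be known, or there must be a stated rule for women whose status is unknown. The protocol places the time point outside its own follow-up and names no follow-up field that holds the status.

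The figure would then depend on unscheduled contacts, and two counting rules are open. One counts only women seen around 9 months, which risks selection because returning may be related to continuing or stopping. The other counts a woman as continuing unless a discontinuation is recorded, which misses discontinuation that never reached the logbook. The protocol does not say which applies.

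Aim 2 uses the Maintenance measures to judge whether the intervention is sustainable, so a continuation figure with a narrow confidence interval and an unknown bias could be over-read.

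**Working it through.** **1. The time windows.** The stated cap reproduces: 40 + 14 = 54 weeks. Nine months is 9 × 365.25 / 12 / 7 = 39.1 weeks. The eligibility window runs "at any stage of pregnancy or up to 14 weeks postpartum", so uptake is taken at delivery, 6 weeks and 14 weeks postpartum.

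| Uptake (weeks postpartum) | 9 months after uptake (weeks postpartum) | Beyond the 14-week cap |
|---|---|---|
| 0 | 39.1 | 25.1 weeks |
| 6 | 45.1 | 31.1 weeks |
| 14 | 53.1 | 39.1 weeks |

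No woman who takes up a method at or after delivery reaches the time point inside the cap. The gap from the 6-week visit is 39.1 − 6 = 33.1 weeks.

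**2. The Table 2 window.** Implementation and woman-level maintenance both run from Y2-1 to Y4-1, which is 5 × 6 = 30 months. Uptake in the last 9 months cannot reach 9 months inside that window. If uptake were uniform over time (assumed), that is 9/30 = 30% of users.

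**3. The interviews.** A woman promoted in gestational week g is interviewed at about week g + 39.1. If she is promoted before delivery and takes up a method at or after it, the interview falls earlier than 9 months after uptake. If g is below 54 − 39.1 = 14.9, it falls within the first 14 weeks postpartum. Even if all 25 interviews were a simple random sample of users at the right time, the 95% half-width at 80% would be 1.96 × √(0.8 × 0.2 / 25) = 0.157, about 16 points. They also include non-users and are analysed thematically.

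**4. Bounds when status is partly unknown.** Table 5 expects 3,687 + 1,399 = 5,086 LARC users in the 12 facilities. Let r be the share with known 9-month status and p the proportion continuing among them. The protocol gives neither, so both are assumed. Lower bound = r·p; upper bound = r·p + (1 − r).

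| r (assumed) | p (assumed) | Lower | Upper |
|---|---|---|---|
| 0.30 | 0.80 | 0.24 | 0.24 + 0.70 = 0.94 |
| 0.60 | 0.80 | 0.48 | 0.48 + 0.40 = 0.88 |
| 0.80 | 0.80 | 0.64 | 0.64 + 0.20 = 0.84 |
| 0.95 | 0.80 | 0.76 | 0.76 + 0.05 = 0.81 |

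At r = 0.60 there are 0.60 × 5,086 ≈ 3,052 women, and the usual 95% half-width is 1.96 × √(0.16 / 3,052) = 0.014. An interval of ±1.4 points would sit beside bounds 40 points wide.

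**5. Direction of bias.** Take a true continuation of 80% (assumed).

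- Only women seen, continuers returning at 60% and discontinuers at 30%: 0.48 / (0.48 + 0.06) = 89%.
- Only women seen, continuers returning at 30% and discontinuers at 90%: 0.24 / (0.24 + 0.18) = 57%.
- No record counted as use, with 90% of discontinuations recorded: 1 − 0.20 × 0.90 = 82%. With 30% recorded: 1 − 0.20 × 0.30 = 94%.

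Counting only women seen can err either way. Counting no record as use errs upward, by an amount that depends on how fully discontinuation is recorded.

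**The case against.** The strongest defence is that a journal article condenses the full protocol. The complete logbook field list, any later follow-up and the rule for unknown status may stand elsewhere. The 54-week limit may describe service delivery only, since it matches the eligibility window and the same sentence mentions interviews 9 months after promotion. The protocol also describes a unique code that follows clients through antenatal care, delivery and infant vaccination, reimbursement for follow-up visits, reminders by community health workers, and a first vaccination visit that implies later ones.

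Part of this stands: the limit need not bar later abstraction of records, and later contacts will occur. But none of these provisions is tied to a status check at 9 months. The pilot's tracking rate above 95% covers only women who attended multiple visits. The government Family Planning logbooks are named only as a source of facility information, age and parity. The conflict is between things the article does state, so it is more than omitted detail.

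A reader might infer more than the text supports:

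- **That the figure will certainly rest on self-selected returners.** The no-record-means-use rule fits the wording equally well.
- **That this second rule would give nearly 100%.** No figure supports that; recorded removals would lower it.
- **That complete-case analysis governs this outcome.** The Missing data section prescribes it for primary analyses, with multiple imputation as sensitivity analysis. Continued use is not presented as primary.
- **That cost-effectiveness is affected.** The economic evaluation section does not name continuation as an input.

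**Conclusion.** The point holds as a conflict within the protocol. The proportion still using a method 9 months after uptake is promised from logbook data, but the scheduled follow-up, the participation cap, the named follow-up fields and the interviews do not provide it. The time gap of 25 to 39 weeks beyond the cap is plain arithmetic from the protocol's own figures.

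The size of any error is not known. The bounds of 24% to 94% and 48% to 88% rest on assumed contact and continuation rates and on LARC users only, whereas the outcome covers every PPFP method. They illustrate how little the data would say at low contact; they do not predict this trial's error. At 95% known status the problem would be small (76% to 81%). The direction of bias cannot be stated.

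Continued use is not marked in Table 1 as used in the power analysis and is treated here as secondary. The analysis of postpartum LARC uptake is unaffected. The sponsor should correct this, but it does not threaten the trial's main result.

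**What to change.** 1. Reconcile the 54-week participation limit and the Table 2 maintenance window with an outcome 9 months after uptake.
2. Add to the PPFP logbook current use and the date of removal, expulsion or switch, recorded at any later clinic or infant-vaccination contact.
3. Fix the denominator as all women who took up a method.
4. Report the share with known 9-month status, and give best- and worst-case bounds beside the observed proportion.
5. Do not make a time-to-discontinuation analysis censored at last contact the main estimate. New fields create no new contacts, and if return is related to stopping, that censoring is informative.
6. If few women have known status, limit the claim to continuation at the scheduled 6-week follow-up.

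The cost is slightly more logbook recording, some analysis wording, and a continuation figure reported with less apparent precision.

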##### Provider level

Drawing from the diffusion of innovation theory [25], we will conduct in-depth interviews with PPFP trainees, CHW, Happy Clients, and all facility directors at the end of the implementation. Interview questions will include perceptions of the degree to which intervention is better than SOC; perceptions about how consistent intervention implementation and the demand creation strategies are with the values, culture, experiences, and needs of pregnant women and partners; the perception that intervention implementation is needed; general perceptions of difficulty of intervention implementation and the demand creation strategy burden/cost on providers or stakeholders; evaluation of facilitators/barriers and suggestions for improvement in intervention implementation (training and service delivery) for future refinement of the implementation strategies; and the extent to which providers and stakeholder feel that the intervention implementation improves health for women and families. During interviews, we will also use a standardized checklist to document ongoing or planned PPFP trainings at the facilities, PPFP promotional activities, continued use of PPFP logbooks, discussion of PPFP at regular staff meetings, and pharmacy coordination with providers to ensure PPFP supplies/stocks.

##### Stakeholder level

We will conduct in-depth interviews among stakeholders including MOH and Rwandan Family Planning Technical Working Group members, clinic directors, and nurse administrators. Interviews will take place at the end of the intervention period and will assess the continued engagement, buy-in, and support for PPFP. To assess the national-level maintenance, we will also assess the progress of the MOH to institutionalize PPFP services via renewed public support/statements, allocation of training funds, or dedicated funding for PPFP.

#### Safety endpoints

PPFP side effects include pelvic pain, heavy menstrual bleeding/menorrhagia, dysmenorrhea, infection, perforation of the uterine wall, pelvic inflammatory disease (PID), headaches, irregular periods, nausea, blood clot, minor bleeding, severe bleeding, and pain.

### Participant timeline {13}

The timeline in Table 2 indicates the schedule of interviews and intervention implementation. Women will participate for a maximum of 54 weeks (40 weeks gestation plus 14 weeks postpartum), and in-depth interviews with women will occur 9 months after PPFP promotions. The timeline for implementation of the cluster-randomized stepped-wedge is shown in Table 3.

**Table 2 Tab2:** Overall timeline of study activities by year (Y) (in 6-month intervals)

Aim	Study activity	Y1-1	Y1-2	Y2-1	Y2-2	Y3-1	Y3-2	Y4-1	Y4-2	Y5-1	Y5-2
1	Protocol development and IRB approvals	*X*									
	In-depth interviews		*X*								
	Facility needs assessments			*X*							
	Implement the intervention in a randomized stepped-wedge design and collect effectiveness and implementation data			*X*	*X*	*X*	*X*	*X*			
2	Evaluate intervention reach, effectiveness, and adoption								*X*	*X*	*X*
	Evaluate the intervention implementation (time-motion studies)			*X*	*X*	*X*	*X*	*X*			
	Evaluate intervention maintenance: women/couples			*X*	*X*	*X*	*X*	*X*			
	Evaluate the intervention maintenance: providers and stakeholders								*X*	*X*	
3	Develop costing tools	*X*	*X*								
	Collect cost data			*X*	*X*	*X*	*X*	*X*			
	Cost-effectiveness analyses and development of costed implantation plan								*X*	*X*	*X*
	Publications, dissemination								*X*	*X*	*X*

**Table 3 Tab3:**
[figure not shown]
Cluster-randomized stepped-wedge design

### Sample size {14}

Table 4 shows the expected number of participants included in each study activity. We assume that the proposed sample sizes shown below for in-depth interviews will allow us to reach saturation. Based on facility volume and preliminary findings, we conservatively expect to deliver PPFP promotions to 12,714 in the 12 intervention facilities (18% of reproductive age women in the catchment area) and 21,383 women/couples total across the 17 facilities (12 intervention plus 5 training facilities).

**Table 4 Tab4:** Expected number of participants included for each study activity

Specific aim	Activity	Total participants
Aim 1	In-depth interviews	12 facility directors 24 nurses in-charge of L&D and family planning 24 CHWs 5 MOH stakeholders
Aim 2	Intervention trainings	98 government facility PPFP promoters 68 community health worker promoters 78 government facility PPFP providers (70 certified) 36 Happy Client promoters
	Intervention recipients	We expect to deliver PPFP promotions to *n* = 12,714 women/couples
	In-depth interviews	25 women/couples 25 providers 25 stakeholders

We assume based on our pilot that promotions will reach 75% of pregnant women in health centers. Also extrapolating from our pilot data, we also expect to insert 3687 PPIUDs and 1399 PP implants in the 12 intervention facilities (6201 PPIUDs and 2352 PP implants total across the 17 facilities) (Table 5). Given the facility volume and previous experience, PPFP service delivery to this number of women is highly feasible. Sample size and power calculations account for intra-cluster correlation (ICC) which considers the between-cluster correlation, within-cluster correlation, and repeated measures. We assume pooled between- and within-cluster ICCs and a homogeneous intervention effect over time. We have > 80% power to detect all differences in the expected proportions shown in Table 5 comparing PPFP intervention to control.

**Table 5 Tab5:** Expected deliverables during the study time period, *n* = 12 intervention facilities. Power to detect the differences between standard of care control and intervention: > 80%

Stakeholders	Control^**a**^			PPFP intervention		
	***N*** events	Denominator	Expected %	***N*** events	Denominator	Expected %^**b**^
Clinic directors engaged	2	12	17%	12	12	100%

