### Trial design {8}

We will implement the intervention in 12 facilities in a clinic-randomized stepped-wedge design. The stepped-wedge design will ensure that each facility receives the intervention over time and provides its own standard of care control, limiting temporal bias. Facilities are high-volume and have similar client volume and staffing-to-patient ratios. Each clinic will be randomized using the SAS random number generator (SAS Institute v9.4, Cary, NC). The allocation ratio will be 1:1. This is a superiority trial.

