#### Effectiveness

##### Primary analyses

We will tabulate, by facility, a total number of all PPFP methods provided and the proportion of PPFP uptake among women who delivered at one of our facilities (overall and by method type). PP LARC uptake (by method type) will be evaluated using logistic regression and general estimating equation methods to account for the clinic-randomized design. The main predictor will be the intervention versus the control arm. For example, the following generalized linear mixed model will compute the adjusted odds ratio for taking up a PP implant: *Y*_*ijl*_ = *β*0 + *β*1 × (intervention_*ij*_) + *β*2 × (covariates_*ij*_) + *β*3 × (intervention_*ij*_ × covariates_*ij*_) + *β4*_*j*_ + *u*_*i*_ + *ε*, where *i* = clusters*, j* = time periods, *l* = individuals, *β*1 = fixed effect for intervention, *β*2 = fixed effects for covariates, *β*3 = fixed effects for interactions, *β*4_*j*_ = fixed effect for time, *u*_*i*_ = random effect for ICC, and *ε*_*ijl*_ = random residual. Covariates assessed as potential confounders will include facility volume, service volume-to-staffing ratio, and number of promotions received. Outcomes will be reported as adjusted odds ratios with 95% confidence intervals. We hypothesize that the intervention will significantly increase PP LARC uptake by comparing intervention versus control. We will also assess the independent effect of each promotional strategy on PP LARC uptake. Every promotion will be recorded and we will estimate the independent effect of receiving CHW counseling, video-based promotions, or Happy Client promotions (treating each strategy as an independent, dichotomous exposure of interest) on PPFP uptake using adjusted multivariate regression modeling with general estimating equations methods.

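### The 12-clinic stepped-wedge model fixes a constant effect and a single ICC and leaves GEE or mixed model open, so intervals can be too narrow and the estimate biased if the effect changes with exposure time

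*Protocol article*

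**What the plan says.** Under Trial design {8}: "We will implement the intervention in 12 facilities in a clinic-randomized stepped-wedge design". Under Sample size {14}, the power calculation is said to allow for clustering, "Sample size and power calculations account for intra-cluster correlation (ICC) which considers the between-cluster correlation, within-cluster correlation, and repeated measures", but the next sentence reads "We assume pooled between- and within-cluster ICCs and a homogeneous intervention effect over time". No ICC value is printed. The claim that follows is "We have > 80% power to detect all differences in the expected proportions shown in Table 5 comparing PPFP intervention to control".

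Under Statistical methods {20a}, Primary analyses, PP LARC uptake "will be evaluated using logistic regression and general estimating equation methods to account for the clinic-randomized design". The text then writes out, as an example, a generalized linear mixed model with one fixed intervention effect, fixed period effects, covariates, intervention-by-covariate interactions, and one clinic term described as "random effect for ICC". It has no term for time since crossover and no clinic-by-period term. The listed covariates are facility volume, staffing ratio and number of promotions, so the interactions do not supply an exposure-time effect.

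Two other statements bear on whether the effect can be constant. Under Eligibility criteria {10}: "Eligible Happy Client promotors will be postpartum women who received promotions and selected a PPFP method". Under Participant timeline {13}: "Women will participate for a maximum of 54 weeks (40 weeks gestation plus 14 weeks postpartum". PPFP service delivery training also requires supervised insertions of both LARC types before a provider is certified.

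**The concern.** There are three separate problems.

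1. **Correlation.** A clinic random intercept makes two women in one clinic equally correlated whether they deliver in the same period or years apart. In a stepped wedge the effect is estimated largely from within-clinic changes over time. Real clinic-by-period variation is then counted as information, and the model's standard error is too small.
2. **Method.** GEE and the mixed model estimate different odds ratios (population-averaged and clinic-specific) and fail differently. A clinic-level sandwich error does not rely on the single-ICC assumption but is too small with 12 clusters. The mixed model relies on that assumption. The text does not say which is primary.
3. **Effect shape.** One coefficient assumes the same effect in every period after crossover. Supervised certification, Happy Clients drawn from women who have already accepted a method, and promotions that accumulate over a pregnancy all make a gradual build-up plausible. The constant-effect estimator gives later exposure periods negative weight, so a changing effect is not simply averaged.

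The size of the odds ratio and its interval are at stake, more for implants than for PPIUDs.

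**Working it through.** **Inputs from the article.** 12 clinics; 17,870 women delivering (Table 5); PPIUD 20/268 = 7.5% vs 3687/12,714 = 29.0%; implant 14/268 = 5.2% vs 1399/12,714 = 11.0% (printed as 10%).

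**Assumptions.** Table 3 is a figure that is not shown and no ICC is printed. I therefore assume equal steps (3, 4 or 6, and 2 in the simulation), equal period sizes and ICC ρ = 0.01 to 0.05, with 0.10 where stated. CAC is the between-period ICC divided by the within-period ICC. The single-ICC model means CAC = 1.

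**Step 1: the plan's own figure.** Ignoring clustering, with a pooled null variance, implant power is Φ[(0.0578 − 1.96 × 0.01922)/0.01387] = Φ(1.45) = 92.7%. PPIUD power is about 100%. The printed counts are compatible with the > 80% claim. With a single ICC (CAC = 1), stepped-wedge power is also about 100% for both methods. The ICC-adjusted figure itself cannot be reproduced.

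**Step 2: standard error of the random-intercept model.** Per clinic, with m women per period:
- model variance ∝ ρJ + [(1−ρ)/m]I
- true variance ∝ ρ·CAC·J + [ρ(1−CAC) + (1−ρ)/m]I

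Putting the model's GLS weights through the true variance gives the ratio of true to model SE. It is close to √[1 + ρ(1−CAC)m/(1−ρ)].

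| Steps | m | ρ | CAC | Approximation | Exact ratio |
|---|---|---|---|---|---|
| 6 | 17,870/84 = 213 | 0.01 | 0.95 | √(1 + 0.0005/0.00465) = 1.05 | 1.05 |
| 4 | 17,870/60 = 298 | 0.05 | 0.80 | √(1 + 0.01/0.00319) = 2.03 | 2.03 |
| 3 | 17,870/48 = 372 | 0.05 | 0.80 | √(1 + 0.01/0.00255) = 2.22 | 2.21 |

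The range is 1.05 to 2.2. At those ends a nominal 5% test rejects 2Φ(−1.96/1.05) = 6% and 2Φ(−1.96/2.21) = 38% of the time.

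**Step 3: simulation.** Implant rates 5.2% vs 11.0%, exchangeable logistic GEE, 2, 4 or 6 steps, ICC 0.05 (0.10 also at CAC 0.8), 600 runs per cell. Coverage of nominal 95% intervals:
- plain sandwich: 87 to 92% at every CAC (SE about 9 to 17% too small)
- single-ICC model-based: 95 to 96% at CAC 1, 72 to 89% at CAC 0.8, 69 to 83% at CAC 0.5
- Mancl-DeRouen SE with t(10): 95 to 97%

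**Step 4: effect shape.** If the effect in exposure period e is δ_e, the constant-effect estimator returns Σ w_e δ_e, where w_e are its GLS weights. With 4 steps and ρ = 0.05, w = 0.992, 0.300, −0.096, −0.196.
- Linear build-up (0.25, 0.5, 0.75, 1): 0.248 + 0.150 − 0.072 − 0.196 = 0.13. True average 0.625. With ρ = 0.01 the result is 0.15.
- Half effect in the first period, then full: 0.496 + 0.300 − 0.096 − 0.196 = 0.50. True average 0.875.
- Waning from full to half (1, 0.833, 0.667, 0.5): 0.992 + 0.250 − 0.064 − 0.098 = 1.08. True average 0.75. With ρ = 0.01 the result is 1.07.
- Constant effect: the weights sum to 1, so there is no bias.

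Negative weights on late exposure periods also appear with 2, 3, 6 and 12 steps.

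**Step 5: power with separate ICCs.** Implant, 4 steps, t(10): 95% (ICC 0.05, CAC 0.8), 72% (0.05, 0.5), 77% (0.10, 0.8) and 46% (0.10, 0.5). PPIUD power stays at or above 94% in these settings.

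**The case against.** A reader might infer that the effect will be understated. The article does not support that as a certainty. Promotion is not only antenatal: women are eligible at delivery, infant vaccination and postpartum services up to 14 weeks, so a woman delivering just after crossover can still be reached. Happy Clients are not required to come from the same clinic. The five training facilities are expected to reach 21,383 − 12,714 = 8,669 women and could supply some, and only 36 are planned. The adverse-event section describes daily supervision in the first month that is later phased to an on-call system, which could produce waning and hence overstatement. All this stands: the direction of bias is conditional.

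A reader might also infer that the standard errors will be uncorrected. That rests on silence. A condensed article may leave small-sample corrections to the analysis plan, and the model is offered as an example. The absence of a correction is therefore not itself a fault, and the GEE result in Step 3 applies only if a plain sandwich error is used. Likewise Table 3 may already show a transition period.

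What the objection does not remove is the written content. The homogeneous effect and pooled ICC are stated for power, the model equation carries both, and the paragraph names two different methods. The two causes of narrow intervals belong to different methods and do not add up.

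On consequences, downward bias is conservative for a superiority claim, and the article does not say that this regression estimate feeds the cost-effectiveness model.

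**Conclusion.** The point holds as a conditional weakness in a stated specification. For the random-intercept model, the true SE is about 1.05 to 2.2 times the model SE if CAC is 0.8 to 0.95; at CAC = 1 there is no such problem. For GEE with a plain sandwich error, 12 clinics give about 87 to 92% coverage. If the effect changes with time since crossover, the constant-effect estimate can be far from the time average: at 4 steps, about 0.13 to 0.15 against 0.625 for a linear build-up, and about 1.07 to 1.08 against 0.75 for waning.

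These sizes rest on assumed ICC, CAC, step counts and effect shapes, and the bias and SE-ratio calculations are on a linear scale. The documents do not establish which shape will occur. The PPIUD contrast is large enough to be detected in the settings tried. The implant contrast, about 6 percentage points, is the one exposed.

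**What to change.** - Name one primary method and state which odds ratio it estimates.
- If it is the mixed model, add a clinic-by-period random effect.
- If it is GEE, use bias-corrected standard errors with a t reference. A permutation test over the randomised crossover order is an alternative.
- Pre-specify a model with exposure-time indicators and report its time-averaged effect as a sensitivity analysis beside the constant-effect estimate.
- State the ICC used and recheck the > 80% power claim over a range of ICC and CAC, at least for implants.

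The cost is wording, modest analysis work and wider intervals. The widening matters little for PPIUD (7% vs 29%) but does matter for implants (5.2% vs 11.0%).

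Making the exposure-time model primary is a debatable trade-off. Its time-averaged estimate has an SE about 1.5 to 1.6 times that of the constant-effect model (3 to 6 steps, ICC 0.05, CAC 0.8), which takes implant power from about 89 to 99% down to about 57 to 76%. For that reason it is proposed here as a sensitivity analysis.
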